**Methods/design:**

We will employ a multi-site, longitudinal, blinded randomized controlled trial (RCT) design with a target sample of 120 patients with age-related cognitive decline. Patients will be asked to complete 36 training sessions remotely (30 min/day, 5 days a week, over 3 months) of either the experimental TAPAT training program or an active control computer games condition. Patients will be assessed on a battery of cognitive and functional outcomes at four time points, including: a) immediately before training, b) halfway through training, c) within forty-eight hours post completion of total training, and d) after a three-month no-contact period post completion of total training, to assess the longevity of potential training effects.

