## Methods

### Overall design and timeline

The current study will employ a multi-site, longitudinal, blinded randomized controlled trial (RCT) design with a target sample of 120 older adults without dementia or MCI (see inclusion criteria below). Sixty older adults completing TAPAT will be compared to sixty older adults completing the active control condition (computer-based games; see Fig. 1). Total participation time is approximately 6 months and includes 5 in-person assessment sessions. Assessments will be performed at University of Iowa (Iowa City, IA) and VA Boston Healthcare System (Boston, MA). The first assessment session (V0) involves screening for eligibility (see inclusion/exclusion below). If the participant is eligible, baseline assessments are administered in a second visit (V1) to characterize their cognitive and functional abilities before training. After the baseline assessment, older adults are randomized to either the TAPAT or control training program and complete approximately 12–16 weeks of in-home training, while monitored and coached by a research assistant (*cognitive remediation coach*). Participants assigned to the experimental software treatment program will be randomly assigned to receive performance feedback (version A.1 vs. A.2) in the first or the second half of training. Participants will then be asked to complete a mid-training assessment (V1.5) and will be administered a subset of assessments comprised of the secondary outcome: mindfulness. At the mid-training assessment, participants who were randomized to the experimental program will switch program versions (i.e., participants that trained on version A.1 will begin version A.2, and vice versa), such that participants train on both versions. To measure potential training-related improvements, participants will be assessed immediately after the completion of the total training (V2) by an assessor that is blind to group affiliation. To measure the persistence of potential training-related improvements, participants are also assessed after a three-month no-contact period (V3), again by an assessor blind to group affiliation. After this visit, participant activities are completed and trial participation ends.

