### Repeated assessment battery

Once a participant is deemed eligible for participation based on their V0 results, they are next scheduled for their baseline session on the repeated assessment battery (V1), which takes approximately two hours. After completing this baseline assessment, participants are randomly assigned to either experimental or control training conditions (see below). Then, following the program set-up visit and after completing the first half of the training sessions, they will be administered an abbreviated mid-training assessment (V1.5) comprised of mindfulness-related measures. Immediately after total training is completed, participants are re-administered the baseline assessment battery (V2) and again after a three-month no contact period (V3).

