### Randomization

Participants will be randomized after the baseline visit and before the planned first day of program use. All V0 and V1 data for each participant must be fully monitored, with all queries resolved, before randomization may take place. We will use a randomization server (sealedenvelope.com) that implements the random permuted blocks within strata procedure [49, 50] with strata as age (*Older Adults 65–74* or *Older Adults* ≥ 75 years of age), allocation ratio is 1:1. Participants who are randomized to the experimental treatment group will also be randomized to either receive version 1 (experimental treatment with performance feedback) or version 2 (experimental treatment without performance feedback); at the mid-training assessment, participants will undergo a reversal of the version type such that all participants completing the entirety of the training will have trained on both versions of the experimental training program. The Site Coordinating Center will issue a randomization assignment at the appropriate time. This approach represents a best practice approach to randomization, implementing an automated centralized group assignment procedure with allocation concealment, and effective separation of sequence generation and allocation concealment.

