**Fig. 3 Fig3:**
[figure not shown]
Version A.1 of TAPAT with performance feedback provide every ~ 2 min in the form of an accumulated score (max = 20 per two minutes; total score max = 100)

All training sessions will consist of the three variations of TAPAT to provide variety during each training session. A summary of the training schedule is provided in Table 1.

**Table 1 Tab1:** Training Schedule for a participant randomized to receive TAPAT with feedback in the first half of training

Sessions 1–18	TAPAT with Feedback (v.A.1)	(32 min/session)
	TAPAT (10 min) > 60 s break> TAPAT (10 min) > 60 s break > TAPAT (10 min)	
V1.5	Mid-training assessment (V1.5) Subset of assessments administered in-person.	
Sessions 19–36	TAPAT without Feedback (v.A.2)	(32 min/session)
	TAPAT (10 min) > 60 s break> TAPAT (10 min) > 60 s break > TAPAT (10 min)	

*Active Control Program (commercially-available computer games):* The active control program is composed of 6 commercially available computer games and is designed to: 1) be a face-valid approach to treating cognitive remediation age-related decline (analogous to crossword puzzles for age-related cognitive decline), ensure that participants remain blind to group affiliation, and match the experimental treatment program in halo or expectation-based influence on performance in neuropsychological outcome measures; 2) match the experimental treatment program in overall program use intensity, time-spent attending, delivered rewards, and overall engagement; and 3) provide a comparison group that matches the experimental treatment group on the aforementioned attributes, but without the known therapeutic elements.

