### Data analysis

The data analysis plan a priori defines a primary intent-to-treat (ITT) population, a set of secondary evaluation populations, a primary outcome measure, a set of secondary outcome measures, a single primary evaluation time point, a secondary evaluation time point, a primary statistical analysis methodology, a criterion for statistical significance, and guidance for interpretation of results. There will be no interim analyses.

The primary ITT population is defined as all participants who complete a set-up (V1) visit. Note that this includes all randomized participants except those who drop/withdraw post-randomization and pre-setup visit. In total, there are three a priori defined analysis populations, including a primary analysis population (i), a secondary analysis populations designed to compare effect sizes in populations with no missing data (ii) and a tertiary analysis population who completed all training visits (iii)i.*Intent to Treat (ITT) population:* This is the a priori primary analysis population, defined as including all randomized participants who completed a V1.ii.*Intent to Treat (ITT) Fully-Evaluable (FE) population:* This is a secondary analysis population, defined as including all members of the ITT population that complete a V2 visit (the ITT-FEV2 population), or all members of the ITT population that completed a V3 visit (the ITT-FEV3 population). Note that a participant may complete a specific visit but have missing data for a test in which case the participants is in the overall FE population but does not contribute data to the FE population for that visit, e.g., the number of evaluable cases for a specific test on a specific visit may be smaller than the FE population for that visit because of missing data.iii.*Intent to Treat (ITT) Fully-Trained (FT) population:* This is a secondary analysis population, defined as including all members of the ITT-FE population who complete a target number of training visits (65 visits). Note that the FT populations are strict subsets of the FE populations; a person who completes the target number of training visits but does not complete the evaluation visit is not a member of the FT population.

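### The Fully-Trained population requires 65 training visits, but only 36 sessions are scheduled, so as written nobody can qualify

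*Protocol article*

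**What the plan says.** The Data analysis section lists three analysis populations fixed in advance. It introduces the third as "a tertiary analysis population who completed all training visits". The numbered definition then gives it a threshold: "all members of the ITT-FE population who complete a target number of training visits (65 visits". The section adds that this group is a strict subset of the Fully-Evaluable population.

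The training schedule is described elsewhere:

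- Abstract, Methods/design, for both arms: "Patients will be asked to complete 36 training sessions remotely (30 min/day, 5 days a week, over 3 months".
- Table 1, for a TAPAT participant who receives feedback first: sessions 1 to 18, the mid-training assessment, then "Sessions 19–36". Nothing is scheduled after that.
- Overall design and timeline: participants "complete approximately 12–16 weeks of in-home training, while monitored and coached by a research assistant". Aims and hypotheses gives the same 12–16 weeks.
- Repeated assessment battery: the mid-training assessment comes "after completing the first half of the training sessions".
- Randomization: TAPAT participants swap program version at that point, so that "all participants completing the entirety of the training will have trained on both versions of the experimental training program".

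**The concern.** The threshold that defines an analysis population is larger than the number of sessions anyone is asked to do. If a training visit is a training session, no participant can meet it, however adherent. The section also disagrees with itself: completing all training and completing 65 visits are different conditions when the schedule holds 36.

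What is at stake is the prespecified analysis of participants who received the full training dose. Followed literally, it has no data, so someone must choose another cut-off. If that choice is made after unblinding, it could be made with results in view, and the benefit of having defined the population in advance is lost.

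A related inconsistency lies in the Abstract. Its session count, weekly frequency and duration cannot all be true, so a reader cannot tell what regimen was prescribed.

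**Working it through.** **Inputs**

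| Quantity | Value | Source |
|---|---|---|
| Fully-Trained threshold | 65 training visits | Data analysis |
| Scheduled sessions, both arms | 36 | Abstract, Methods/design |
| Session numbering | 1–18 and 19–36 | Table 1 |
| Stated frequency and duration | 5 days a week, 3 months | Abstract, Methods/design |
| Training duration | 12–16 weeks | Aims and hypotheses; Overall design and timeline |
| In-person assessments | 5 | Overall design and timeline |
| Adherence check-ins | weekly | Foreseeable risks |
| Depression and suicidality assessments | baseline, week 13, week 26 (end of study) | Foreseeable risks |

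**1. Scheduled total.** Table 1 gives 18 + 18 = 36, which agrees with the Abstract.

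**2. Can 65 be reproduced?**

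- Sessions as scheduled: 36.
- Sessions + 5 assessments + 1 set-up visit: 36 + 5 + 1 = 42. The article also attaches the set-up label to V1, so the extra 1 may be a double count; it is kept here to be generous.
- Adding weekly check-ins over the longest course, 16 weeks: 42 + 16 = 58.
- Counting the three 10-minute blocks in each session: 3 × 36 = 108.
- Frequency × duration: 5 × 12 = 60, 5 × 13 = 65, 5 × 16 = 80.

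Only 5 a week for 13 weeks gives 65, and that contradicts the stated 36 sessions. That 65 arose this way is an inference; the article does not say so. The wider counts are in any case generous, because the definition of this population treats the evaluation visit as separate from training visits.

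**3. Size of the gap.** 36/65 = 0.554, a shortfall of 65 − 36 = 29. With assessments and set-up counted, 42/65 = 0.646. With weekly check-ins as well, 58/65 = 0.892. No count of contacts up to this maximum reaches 65.

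**4. Frequency in the Abstract.** 36 sessions ÷ 5 a week = 7.2 weeks, against 3 months in the same sentence. Spread over the stated durations, 36/12 = 3.0, 36/13 = 2.77 and 36/16 = 2.25 sessions a week.

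**5. Which figure is out of line?** The 36 stands in two places, the Abstract and Table 1. The duration of about 3 months is supported by the 12–16 weeks in two sections and by the calendar. With 7.2 weeks of training and about 13 weeks without contact, the study would end near week 20 (7.2 + 13 = 20.2). With 13 + 13 = 26 it ends at week 26, as stated. The 65 visits and the 5 days a week each appear only once. The switch at the half-way point gives 18/18 with 36 sessions but 32.5 with 65; this is minor support, since equal halves are shown only in Table 1.

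**The case against.** The strongest case on the other side does not deny the contradiction. It questions which number is wrong and how much it matters.

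- **The evidence for 36 is not one-sided.** A 12–16 week course at 5 a week is 60 to 80 sessions, a range that contains 65, and an assessment at week 13 fits 5 × 13 = 65. This stands in part: duration alone does not separate the two numbers. But week 13 fits 36 sessions equally well, and Table 1 numbers the sessions explicitly and stops at 36. The case for 36 rests mainly on Table 1 and the Abstract's count.
- **The Abstract's three figures are merely inconsistent; none is shown to be the error.** Taken alone, that sentence does not settle it. Read with the rest of the article, the session count and the duration are each corroborated and the frequency is not. Its fit with 65 is still a good reason to ask the sponsor first.
- **A rate of about 3 days a week is stated nowhere.** True. It is derived from 36 sessions over 12–16 weeks.
- **The impact is small.** This population is called tertiary and then secondary, no test or success claim is tied specifically to it, and the description of completing all training already points to the intended rule. All of this stands. It limits the weight of the point, but a defined population that nobody can enter still needs correcting.
- **The article condenses a fuller protocol that may have the right number.** Possibly, but this is not an omission. The article states two figures that conflict.

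**Conclusion.** The point holds. As written, the Fully-Trained population has 0 members out of up to 120, because full adherence yields 36 of the 65 visits required (55%). This assumes that a training visit is a training session and that nobody trains beyond the schedule. The article offers no other definition and provides for no extra sessions.

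The consequence is confined to one non-primary population. The intention-to-treat analysis, the Fully-Evaluable populations and the planned sample size do not depend on the threshold. Both arms share the regimen, and no bias between arms is shown. The frequency in the Abstract is a minor accompanying correction that drives no analysis. This should be fixed, but it does not threaten the primary result.

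**What to change.** Confirm the delivered schedule with the sponsor. Then, before unblinding:

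1. In the Data analysis section, change the Fully-Trained target from 65 training visits to 36 training sessions. This matches both the section's own description of the population and Table 1. Every evaluable participant who completes the schedule then qualifies.
2. In the Abstract, replace the 5 days a week with about 3 days a week (36 sessions over 12–16 weeks), for both arms.

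If the sponsor confirms that 65 sessions were delivered, keep the threshold and correct the Abstract's session count and Table 1 instead. That is a somewhat larger edit, since the session numbering and the half-way switch would have to be restated.

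In the expected case the cost is one number and one phrase. Visits, staffing, participants, sample size and the primary analysis do not change.

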### Foreseeable risks, Risk Management & Emergency Response

Participation in the study presents minimal risk. The probability and magnitude of harm or discomfort anticipated in this research study are not greater than those ordinarily encountered in daily life or during the performance of routine physical or psychological examinations or tests. Study participation may be discontinued when a participant voluntarily withdraws from the study (e.g. due to scheduling issues or changing residence) or when they express discomfort with any of the study procedures (e.g. excessive frustration, boredom, or eye strain). To improve adherence to the interventions, weekly check-ins were performed to monitor participants’ progress, motivate and provide feedback, and allow participants to voice any adverse effects.

Serious adverse effects from prior studies of the treatments under study have not been reported. The protocol details potential risks related to study participation and includes assessments of depression and suicidality at baseline, week 13, and week 26 (end-of-study). Participants will be encouraged to report any adverse effects occurring during the duration of the study to the point of contact within research staff. PSC does not provide compensation for research-related injuries and will not reimburse or pay medical expenses for the treatment of research-related injuries.

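### The Fully-Trained population requires 65 training visits, but the stated course is 36 sessions, so under that schedule nobody can qualify

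*Protocol article*

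**What the plan says.** The Data analysis section of the protocol article defines three analysis populations in advance. Its overview calls the third "a tertiary analysis population who completed all training visits". The itemised definition then restricts it to fully evaluable participants "who complete a target number of training visits (65 visits"). It adds that someone who reaches the target but misses the evaluation visit is not a member.

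The length of the course is given in two other places:

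- **Abstract, Methods/design:** "Patients will be asked to complete 36 training sessions remotely", for either arm, at 30 minutes a day, "5 days a week, over 3 months".
- **Table 1 (training schedule):** sessions 1 to 18, the mid-training assessment, then "Sessions 19–36". No later session is listed.

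Two further statements bear on the timetable. Overall design and timeline gives roughly 12 to 16 weeks of home training and states: "Total participation time is approximately 6 months and includes 5 in-person assessment sessions". The section on foreseeable risks schedules "assessments of depression and suicidality at baseline, week 13, and week 26".

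**The concern.** The overview makes the target the complete course, so the number in the definition should equal the number of scheduled sessions. It is 65 where the schedule has 36. Nothing in the article schedules sessions beyond 36, explains the 65, or defines a training visit as a unit smaller than a session.

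An analysis population is fixed in advance to remove discretion. This rule cannot be applied literally under the stated schedule, so someone would have to choose another cut-off once adherence data exist, and possibly once outcomes are known. This is also the only predefined set that isolates participants who received the whole dose, and the reader cannot tell which dose that is.

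**Working it through.** **Inputs**

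- Fully-Trained threshold: 65 (Data analysis, population iii).
- Scheduled sessions: 36 (abstract, both arms); 18 + 18 (Table 1).
- Cadence and duration: 5 days a week over 3 months (abstract); 12 to 16 weeks (Overall design and timeline).
- Session length: 30 minutes (abstract); 32 minutes with breaks (Table 1).
- In-person assessment sessions: 5 (Overall design and timeline).
- Total sample: 120.

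**1. Can 65 be reproduced from the schedule?** Table 1 gives 18 + 18 = 36, which agrees with the abstract and fits the switch of program version at the midpoint. It does not give 65.

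**2. Shortfall.** 65 − 36 = 29 sessions more than are scheduled. 65/36 = 1.81, and 36/65 = 0.554. Perfect adherence reaches 55% of the threshold, so under the 36-session schedule the set contains 0 of 120.

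**3. Does another way of counting reach 65?**

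| Count | Total |
|---|---|
| Training sessions | 36 |
| Plus 5 in-person assessment sessions | 41 |
| Plus 1 set-up visit and 16 weekly check-ins (the most that 16 weeks allows) | 36 + 5 + 1 + 16 = 58 |
| 10-minute blocks, three per session | 36 × 3 = 108 |

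None gives 65. The first three fall short of it, and a 10-minute block is not a visit.

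**4. Does the cadence fit?** At five sessions a week, 36 sessions take 36/5 = 7.2 weeks, not 3 months. Spread over the stated training period, 36/16 = 2.25 to 36/12 = 3.0 sessions a week. In the other direction, 5 × 12 = 60, 5 × 13 = 65 and 5 × 16 = 80. The figure of 65 is therefore exactly five a week for 13 weeks, and a safety assessment falls at week 13. That is a likely origin of the number, but it is an inference.

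**5. Dose.** At 30 minutes a session, 36 × 0.5 = 18.0 h is scheduled and 65 × 0.5 = 32.5 h is required. At Table 1's 32 minutes, 36 × 32/60 = 19.2 h and 65 × 32/60 = 34.7 h. The ratio of 1.81 is the same.

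**The case against.** The strongest reply is that 36 may be the wrong number. The abstract's five days a week over 3 months implies about 60 to 65 sessions, so the same sentence that states 36 also supports 65. If 65 is right, the threshold is sound and the set need not be empty. This stands as a limit on the conclusion: the empty set is conditional on the 36-session schedule. It does not remove the contradiction. Against it, 36 appears independently in the abstract and in Table 1 and matches the midpoint switch. Table 1 shows only one sequence of the experimental arm, but the abstract applies 36 to both arms.

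A second reply is that the words visit and session may not mean the same thing. The article uses the term training visit only in this section. The counts above show that no combination of contacts it describes reaches 65.

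A third reply concerns weight. The article describes no specific analysis on this population, no success criterion depends on it, and an analyst could recover the intent from the overview and apply the full-course rule. That is fair, and it limits the importance of the point. What remains is that the cut-off would be settled after data exist instead of beforehand, and that the intent gives no number until the length of the course is itself settled.

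**Conclusion.** The concern holds. The threshold of 65, the count of 36 sessions, and the cadence of five a week over 3 months cannot all be true. If the 36-session schedule is followed, the Fully-Trained population is empty and any analysis planned on it has no data. This rests on two readings: that a training visit is a training session, and that the schedule in the abstract and Table 1 is the one delivered. Confidence is high that the statements conflict; the document does not settle which number is wrong.

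The reach is limited. The definition calls this population secondary and the overview calls it tertiary. The primary intent-to-treat analysis at the post-training visit and the sample size of 120 do not use the threshold. It should be fixed, but it does not threaten the main result.

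**What to change.** Confirm the intended number of sessions from the full protocol or the program configuration, then align three statements before unblinding.

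- **If 36 is right:** define the Fully-Trained population as evaluable participants who complete all 36 scheduled sessions. Replace the abstract's cadence with about 2.25 to 3 sessions a week over 12 to 16 weeks.
- **If 65 is right:** keep the threshold and correct the session count in the abstract and in Table 1, including the midpoint at which the program versions switch.

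In either case use one term, session or visit, throughout. The change is wording in the protocol and the analysis plan. It needs no new data and alters neither the primary analysis nor the sample size.
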